### Pre-randomization procedures

#### Screening

Participants will be recruited from inpatient units at several Minneapolis area hospitals (Hennepin County Medical Center, MHealth Fairview University of Minnesota Medical Center, MHealth Fairview Southdale, Abbott Northwestern, North Memorial). We will assess most inclusion/exclusion criteria via review of the patient’s electronic medical record and self-report. If ACS diagnosis status is unclear in the medical record, staff will review the case with a study cardiologist at that site. If there is an indication of cognitive impairment in the patient chart or if the patient exhibits potentially impaired cognitive function at time of recruitment, staff will complete the Mini-Mental State Exam [43] (MMSE; scores of ≤ 20 will be excluded).

#### Informed consent

Participants that appear to qualify based on medical record review will be approached by research staff. At first contact, study staff will provide an overview of procedures and ask if the participant is willing to be screened. If the patient agrees to be screened and meets inclusion/exclusion criteria, they will be invited to participate. Informed consent will be obtained from participants before any further study procedures. As part of the consent process, we will ask five questions about the study to confirm patient understanding. Patients who answer fewer than four questions correctly (after two tries) will be considered to lack the capacity to consent. All participants will provide informed consent per protocols approved by the Hennepin Healthcare Research Institute IRB (HSR#17-4375). Any changes to the consent protocol will also be approved by the IRB before implementation. All participants will provide written informed consent either via paper or e-consent. It is expected most patients will be consented prior to hospital discharge using paper forms. However, if interested patients are discharged from the hospital before the consent process is complete (see Timing of Pre-Randomization Activities Relative to Hospitalization Section below), patients will be offered the option of documenting their informed consent electronically through Research Electronic Data Capture [48, 49] (REDCap). Only research study staff with training regarding the consent process will obtain consent. The full consent document is provided in additional file 2.

#### Baseline measures

After consent, participants will complete an initial baseline assessment (i.e., “Baseline 1”; See Table 1) consisting of interview questions and self-report questionnaires. Socio-demographic variables collected by self-report at baseline will be used to describe the sample and include: age, gender, ethnicity, employment, and income. Medical history will be assessed through self-report and chart review and will include: (1) diagnosis, treatment, and length of stay for current admission; (2) detailed history of cardiac disease, events, procedures, and treatments (e.g., revascularization); and (3) co-morbid conditions. Smoking history, including current and past smoking, age of smoking onset, and average number of cigarettes per day will be assessed via a self-report. Use of other tobacco products will be assessed by self-report. Nicotine Dependence will be measured using the Fagerström Test for Nicotine Dependence [50] (FTND). Motivation to quit will be measured using the contemplation ladder [51]. A second, brief baseline assessment will be conducted 1 week following hospital discharge and immediately prior to randomization to condition (i.e., “Baseline 2,” See Table 1). This assessment will include assessments of motivation to quit/stay quit [51] and nicotine withdrawal as baseline variables [52]. Both Baseline 1 and Baseline 2 assessments include assessments of outcome variables (see Table 1 for timing, see outcome measures sections below for a full description of all outcome variables).

#### Timing of pre-randomization activities relative to hospitalization

All participants will be initially identified as potentially qualifying during their in-patient stay for ACS or ACS treatment and, in general, participants will complete screening, consent, Baseline 1, and the initial treatment session before discharge from the hospital. However, discharge timing following an ACS can be unpredictable and there are several clinical activities that must occur before discharge (e.g., phase 1 cardiac rehabilitation); thus, the window for research activities is often narrow. Further, COVID-19 related restrictions (starting on 3/17/2020) on research staff entering inpatient rooms have varied across our recruitment sites and over time. Due to these challenges, when necessary, patients will be allowed to complete activities meant to be completed inpatient up to 1 week following discharge (see Table 2).

#### Randomization

Randomization will occur 1 week after hospital discharge, immediately after the Baseline 2. We will stratify randomization on elevated symptoms of depression (Patient Health Questionnaire [53] [PHQ-9] score of ≥ 10 vs. < 10 as measured immediately prior to randomization), use of the study provided nicotine patch between discharge and randomization (i.e., using patch vs. not using patch), and recruitment site (i.e., recruited at primary hospital site vs. hospitals subcontracted for recruitment). The randomization sequence will be generated using a stratified permuted block randomization procedure, with small, random sized blocks. The sequence was generated by the study biostatistician. Only the biostatistician and database manager will have access to the randomization sequence and all other study personnel will remain blind to this sequence. Counselors will randomize participants immediately before initiating Session 2 by entering the participant’s identification number, PHQ-9 score, use the nicotine patch, and recruitment site into REDCap [48, 49]. The REDCap interface will indicate the treatment assignment and the counselor will immediately inform the participant of their treatment condition.

### Treatment conditions

#### Behavioral activation treatment for cardiac smokers (BAT-CS)

BA has its underpinnings in the behavioral model of depression [54], which purports that depression results from reduced engagement in positively reinforcing activities. For participants, this condition will be referred to as the *“Smoking Cessation and Mood”* condition. All of BAT-CS will be delivered by tobacco treatment specialist counselors. BAT-CS consists of 1 in-hospital session and 5 post-discharge sessions over 12 weeks. Session 1 will always occur following informed consent, enrollment, and the Baseline 1 assessment. In general, Session 1 will occur during the ACS hospitalization. However, as noted above, enrollment will be allowed up to 1 week following discharge if not feasible during the inpatient stay. In these cases, Session 1 will occur as soon as possible following discharge and will be conducted in-person at the study outcomes center, in-person at the patient’s home, by video conference, or by telephone (based on participant preference, participant ability to travel, and relevant COVID-19 related restrictions at the time). The same delivery options will be offered for session 2 (1 week post discharge). Sessions 3–6 (at 3-, 6-, 9-, and 12-weeks post-discharge) will only be offered by phone or video conference.

If medically approved (i.e., cleared by participant’s provider or study cardiologist), 8 weeks of nicotine patches will be offered at no cost to the participant. Disinterest in or medical contraindication to the patch is not an exclusion criterion for the study. Patch dosing will follow clinical guidelines and FDA instructions. Patches will be provided to participants in the hospital with instructions to use study patches at discharge. Participants recruited after discharge will be provided with patches as soon as possible after discharge via home drop-off or overnight mailing. If a participant is not interested in nicotine patches at the time of enrollment, 8 weeks of patches will be provided upon request at any time during treatment (i.e., 12 weeks post-discharge) with medical clearance. Participants reporting significant side effects due to the patch will be advised to discontinue use until they can review with their medical provider, or a study cardiologist can provide guidance.

##### Session 1 (50 mins)

Session 1 will occur in hospital whenever possible. Session 1 will be guided by the current clinical practice guidelines [55] and the National Cancer Institute’s *Clearing the Air* patient workbook [56], which the participant will keep. The counselor will provide a strong and personalized recommendation to quit and will discuss (1) past attempts to quit, reframing these attempts as learning opportunities, (2) the risks of smoking and benefits of quitting in general and for cardiac patients, (3) personal reasons for quitting, (4) how to recognize and problem-solve smoking triggers, (5) how to elicit support for quitting, (6) tips for managing cravings, (7) planning for a quit date (i.e., how to remove cigarettes and paraphernalia), and (8) the safety and efficacy of the nicotine patch. Per treatment guidelines [55], brief motivational strategies will be provided to those who remain ambivalent about quitting. Participants ambivalent about quitting may set intermediate goals (e.g., reduction of cigarettes; stop smoking inside home).

##### Session 2 (50 mins)

Session 2 will begin assessment of smoking status, nicotine patch use, and degree of motivation to quit/stay quit, and a discussion of between session mood. If the participant is abstinent, the counselor will reinforce their effort, discuss times since last session when participant struggled with cravings, review strategies for managing triggers and cravings, and problem-solve upcoming challenges to staying quit. If the participant is smoking, the counselor will reinforce any efforts that the participant made (i.e., cutting down), discuss cause of relapse and problem-solve potential solutions to avoid that cause in the future, and utilize brief motivational strategies to prompt another quit attempt. If the participant is willing, the counselor will assist in planning a new quit attempt.

The counselor will also introduce BA mood management in session 2. The importance of addressing depressed mood after a hospitalization for ACS and the rationale for BAT-CS (i.e., loss of valued activities causes depressed mood; poor mood can interfere with smoking cessation) will be discussed with the participant. Next the counselor will conduct a values assessment to guide future activation goals [57]. Specifically, the counselor will review several life areas (e.g., family, work, etc.) and ask the participant to identify any strongly held values in each area (e.g., Family: “I value being a responsible grandparent”). The discrepancy of these strongly held values with continued smoking will be discussed (e.g., “How will continued smoking detract from grandparenting?”). The participant’s reported values will be returned to throughout treatment as motivators for adherence to activation goals and smoking cessation. The counselor will also assess for pleasant/valued activities the participant has given up or severely restricted post-ACS and discuss potential replacements for these losses.

The participant and counselor will then collaboratively set 2–4 activation goals to be completed before the next session. These goals will be guided by the values assessment, replacement of any restricted activities, and consistency with a non-smoking lifestyle. All goals will be within current physical abilities and will take into account that the participant is trying to quit smoking (e.g., goals should not involve increased contact with smoking triggers). The counselor will help problem-solve barriers to goal completion using established BA techniques (e.g., stimulus control, accessing social support) to maximize likelihood of completion. At the end of session 2 the counselor will provide a written list of stated values and immediate activation goals. With the participant’s permission, study staff will send an email or text message between sessions to remind and encourage the patient to complete their goals.

The participant will also be provided with an American Heart Association patient education booklet entitled *After Your Heart Attack*, focused on recommendations for life after an ACS [58]. This booklet is for the participant to review outside of session and is provided to the BAT-CS group so that all participants receive the same health education materials.

##### Sessions 3–6 (30 min)

Sessions 3–6 will follow the same basic format: (1) assess nicotine patch use, smoking status and degree of motivation to quit/stay quit, and provide brief motivational strategies for those still smoking or continued support to those quit; (2) assess and discuss mood since last session; (3) review adherence to activation goals from the previous session; (4) choose 2–4 activation goals that are pleasant and/or in line with the participant’s values and explicitly schedule these; (5) problem-solve barriers to completion of new goals, and (6) offer an automated email or text message reminder of goals. During the final counseling call (week 12), rather than assigning new activation goals, the counselor will guide the participant in continuing to work towards activation goals and smoking abstinence following termination of counseling.

#### Control condition

Consistent with the Pragmatic Model for Comparator Selection in Health-Related Behavioral Trials [59], we chose our control group based on the purpose of the study. Because the purpose of this trial is to demonstrate if providing BA based mood management specifically (rather than increased supportive counseling contact more generally) improves outcomes, we chose an attention control condition.

For participants, this condition will be referred to as the “*Smoking Cessation and Health*” condition. All control condition components will be delivered by the same tobacco treatment specialist counselors providing BAT-CS sessions. The control condition fully controls for contact time in post-discharge sessions by providing cessation counseling plus health and wellness education. All control condition sessions will parallel BAT-CS sessions in terms of session length, timing, and medium of administration.

Participants randomized to control will receive an in-hospital session 1 (50 min.) identical to that received in the BAT-CS condition, including being offered 8 weeks of the nicotine patch free of charge when medically appropriate (see detailed description of Session 1 content above). At each post-discharge session (1, 3-, 6-, 9-, and 12-weeks post-discharge) control participants will receive the same smoking cessation-focused content as the BAT-CS group, but will not be provided with any BA components (i.e., no values assessment, structured goal setting, or focus on the interaction of smoking and mood).

During session 2 in the control condition, participants will revive smoking cessation content, followed by health education focused on life after an ACS. This education will be guided by a booklet from the American Heart Association entitled *After Your Heart Attack*
[58], which provides an overview of why a heart attack happens, what happens after a heart attack (i.e. medications, lifestyle changes, cardiac rehabilitation), emotional responses to having a heart attack, and provides strategies for preventing future cardiac events, including medication adherence, weight management, smoking cessation, limiting alcohol intake, and engaging in physical activity. For sessions 3–6 in the control condition, participants will choose one of the following health topics to discuss: (1) Heart Healthy Nutrition, (2) Fruits and Vegetables, (3) Sleeping Well, (4) Screenings and check-ups, (5) Staying Hydrated, and (6) Communication with your providers. Previous work by our team using similar health education content showed it has no significant effect on mood during smoking cessation [60]. Each education component will be explicitly linked to cardiac health as the content is introduced. To maintain the integrity of our independent variable, we chose topics that are relevant to cardiac health, but do not directly address mood or smoking cessation.

### Outcome assessments

Comprehensive outcomes assessments will be conducted in person, by phone, or using video conference at end of treatment (12 weeks after discharge) and 6, 9, and 12 months after discharge. Abbreviated phone assessments will be conducted by phone at 18-, 24-, 30-, and 36-months post discharge. Assessments through 12 months post-discharge will include biochemical verification of self-reported smoking status. Abbreviated assessments after 12 months will only collect self-reported smoking status.

#### Smoking outcomes

The primary outcome related to smoking will be 7-day point prevalence abstinence (i.e., no smoking at all in the past 7 days, not even a puff), which will first be assessed by self-report. If participants self-report ≥ 7-day abstinence, we will bio-verify their self-report. Saliva cotinine will be the primary bio-verification method (saliva cotinine of less than < 10 ng/ml will be considered abstinent) [61]. Saliva will be obtained from participants using the passive drool collection method and processed by Salimetrics using the salivary cotinine assay to determine the cotinine level present in the sample [62]. Participants will be instructed by research staff on how to prepare for and provide a sample of approximately 0.5 ml of passive drool. For those using nicotine replacement or noncombustible tobacco products, a carbon monoxide (CO) breath sample will be used to verify abstinence (CO < 6 ppm will indicate abstinence [61, 63]). Saliva samples and CO breath samples will be collected by mail if a face-to-face meeting is not possible. In person CO samples will be collected by research staff using the Covita Micro + Basic Smokerlyzer device [64] and remote CO samples will be collected using the Covita iCO Smokerlyzer [65], with telephone guidance provided by study staff. Secondary smoking outcomes will be 30-day point prevalence abstinence, continuous abstinence since discharge, and time from discharge to lapse (i.e., first puff) and relapse (i.e., smoking 7 consecutive days or in two consecutive 7-day periods). Participants who report using other combustible tobacco products will be considered smoking. Use of e-cigarettes and other non-combustible tobacco products (e.g., chewing tobacco) will be assessed at each timepoint and reported, but will not affect determination of abstinence.

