### Aim I

Test the efficacy of BAT-CS versus control on depressed mood and smoking cessation. *Hypothesis 1a*: Patients treated with BAT-CS will demonstrate significantly greater improvements in mood and significantly higher rates of biochemically verified 7-day point prevalence abstinence over 12 months than control patients. This trial is powered for hypothesis 1a analyses. *Hypothesis 1b*: Patients treated with BAT-CS will also have higher rates of 30-day point prevalence and continuous abstinence since discharge and longer time to smoking lapse and relapse than control patients.

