### Participants

ACS is defined as a diagnosis of unstable angina, ST-elevation myocardial infarction, or non-ST-elevation myocardial infarction. ACS will be confirmed by coronary angiogram before enrollment. If diagnosis in the medical record was unclear or contradictory, a study cardiologist will review the case. Only Type I myocardial infarctions will be included (Type II myocardial infarctions caused by demand ischemia will be excluded). Myocardial infarction caused by spontaneous coronary artery dissection (SCAD) was included. We included SCAD cases because SCAD is associated with high rates of both smoking [39] and depression [40]. SCAD is also increasingly considered under the umbrella of ACS [41] and some have argued it should considered a cause of Type I myocardial infarctions [42]. Further, because SCAD occurs primally in women [41], including SCAD will improve gender balance in our study.

Individuals will be identified for recruitment while hospitalized on an inpatient unit for an ACS event. The hospitalization context can include both the initial emergency treatment for the ACS event, as well as subsequent hospitalizations within 30 days of the ACS event related to ACS treatment (e.g., returning to the hospital for bypass surgery). Additional inclusion criteria include (1) smoking ≥ 1 cigarette per day before hospitalization, (2) willing to consider quitting smoking at discharge, (3) age of 18–75, (4) English fluency, (5) lives within a 1.5 h drive from study site or willing to do all post-discharge study procedures remotely, (6) has regular access to a telephone or is willing and able to use a study issued cell phone, and (7) willing to consent to all study procedures. See Table 2 for a history of changes to inclusion criteria during the study.

**Table 2 Tab2:** Major protocol changes

Description	Date
Remuneration for counseling sessions 3–6 was added to protocol based on participant feedback that their participation was limited because phone calls were using up limited cell phone minutes	11/12/2018
Provision of study issued cell phones to participants without other telephone access was added to the protocol to increase recruitment	7/31/2019

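### Time to first lapse is counted from discharge but randomisation is a week later, so week-1 lapses dilute a secondary hazard ratio

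*Protocol article*

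**What the plan says.** All under Protocol article, Methods, unless noted.

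- **Outcome clock.** Smoking outcomes lists "time from discharge to lapse (i.e., first puff) and relapse (i.e., smoking 7 consecutive days or in two consecutive 7-day periods" as secondary outcomes. Hypothesis 1b (Aim I) expects BAT-CS patients to have higher rates of "continuous abstinence since discharge and longer time to smoking lapse and relapse than control patients".
- **Allocation.** Randomization: "Randomization will occur 1 week after hospital discharge, immediately after the Baseline 2". It adds: "Counselors will randomize participants immediately before initiating Session 2".
- **Care before allocation.** Control condition: "Participants randomized to control will receive an in-hospital session 1 (50 min.) identical to that received in the BAT-CS condition".
- **Start of the experimental component.** Session 2: "The counselor will also introduce BA mood management in session 2".
- **Smoking before allocation is foreseen.** The Participants section asks only for willingness to consider quitting, not for abstinence. Session 1 says: "Participants ambivalent about quitting may set intermediate goals". Session 2 describes what the counselor does if the participant is already smoking.
- **Analysis.** Secondary outcome analyses specifies a Cox model with intervention assignment among the covariates, and states no delayed entry and no restart of the clock. Missing data says that everyone randomised is analysed.
- **Data.** Table 1 records smoking since last contact at Baseline 2.

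**The concern.** The arms cannot differ before Session 2, yet the lapse clock has by then been running for a week. Anyone who takes a puff in that week has the event before being allocated. In the Cox model these events have an expected hazard ratio of 1. Hazards are therefore non-proportional by construction: ratio 1 in week 1, the treatment effect afterwards. The fitted ratio is an average of the two.

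At stake is a weakened and harder-to-interpret test of time to first lapse in hypothesis 1b. To a lesser degree, the relapse and continuous-abstinence contrasts under the same hypothesis are affected too.

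**Working it through.** **No plan figure to reproduce.** The article gives no event count or power for lapse, relapse or continuous abstinence. Aim I says that the trial is powered for hypothesis 1a only.

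**Inputs from the article:** N = 324 (taken as 162 per arm), alpha 0.05 (used as two-sided), randomisation one week after discharge.

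**Assumed inputs:**
- q, the share with a first puff in week 1, the same in both arms: 10% to 50%.
- Setting A: 29% vs 37% lapse-free at 12 months among those not lapsed at randomisation. These are the 7-day abstinence rates in the Power section, borrowed for illustration. HR = ln 0.37 / ln 0.29 = 0.80.
- Setting B: control hazard 0.006 per day over 365 days, HR 0.70.

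**First lapse, formula.** Let F be the average proportion lapsing after randomisation among those still abstinent. The share of events after allocation is

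f = (1 − q)F / [q + (1 − q)F],

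and log HR(from discharge) ≈ f × log HR(true).

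- Setting A: F = 1 − (0.29 + 0.37)/2 = 0.67. At q = 20%, f = 0.536/0.736 = 0.73, and exp(0.73 × ln 0.803) = 0.85.
- Setting B: F = 1 − (e^−2.19 + e^−1.533)/2 = 1 − (0.112 + 0.216)/2 = 0.836. At q = 20%, f = 0.669/0.869 = 0.77, and exp(0.77 × ln 0.70) = 0.76.

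**First lapse, simulation** (1,500 trials per setting). It agrees with the formula. Power is shown as clock from discharge vs clock from randomisation among those not yet lapsed.

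| q | A: f | A: HR from discharge | A: power | B: f | B: HR from discharge | B: power |
|---|---|---|---|---|---|---|
| 10% | 0.86 | 0.83 | 30% vs 34% | 0.88 | 0.73 | 74% vs 78% |
| 20% | 0.73 | 0.85 | 23% vs 30% | 0.77 | 0.76 | 62% vs 73% |
| 30% | 0.61 | 0.87 | 18% vs 26% | 0.66 | 0.79 | 49% vs 68% |
| 50% | 0.40 | 0.92 | 13% vs 21% | 0.46 | 0.85 | 28% vs 54% |

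With the clock at randomisation, the estimate stays at about 0.80 (A) or 0.70 (B) for every q. With 10% vs 15% lapse-free instead, a true HR of 0.82 becomes 0.85 / 0.86 / 0.88 / 0.91 at the same four shares.

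**Relapse.** Seven consecutive smoking days can at the earliest just be completed by randomisation. The route through two consecutive 7-day periods cannot be. Few relapse events can therefore precede allocation, although smoking days in week 1 still count towards one soon afterwards.

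**Continuous abstinence.** This is analysed with a logit model, so the hazard-ratio argument does not carry over. Each arm's rate is multiplied by (1 − q). From 29% vs 37%:

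- The difference of 8.0 points becomes 8.0 × (1 − q) = 7.2 / 6.4 / 5.6 / 4.0 points at q = 10 / 20 / 30 / 50%.
- The OR moves from 1.44 to 1.41 / 1.39 / 1.37 / 1.34.
- In a single-time comparison of proportions, power is 29 / 26 / 22 / 16%, against 31 / 28 / 25 / 19% when restricted to those not lapsed: a loss of about 1 to 3 points.

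**The case against.** **Discharge is a sensible clinical origin.** Entry turns on willingness to consider quitting at discharge, study patches are meant to be used from discharge, and follow-up visits are timed from it. Abstinence since that point is easy to interpret. This stands as a reason to keep reporting it, above all for continuous abstinence. It does not make week-1 lapses informative about BAT-CS.

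**The size is assumed.** The week-1 share, both hazard ratios and the hazard are not in the article as values for lapse. This stands. With a low share the loss is small: in setting B at 5% lapsed, the HR is about 0.71 and power is 79% vs 82%. In setting A the change gains only 4 to 8 points (34 − 30, 30 − 23, 26 − 18, 21 − 13) and power stays low.

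**The Cox model may already handle it.** The covariates are written X(t), which would allow assignment to switch on at randomisation. But that is generic notation, and nothing in the text says it is used this way. It would also not change continuous abstinence.

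**Restricting the sample departs from the all-randomised rule.** It does, and the departure must be declared. The comparison remains randomised, because the subset is fixed by Baseline 2 status before allocation.

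**Stronger readings.** A reader might infer that the clock biases the trial towards one arm or produces false positives. It does not: week-1 events occur before allocation and are balanced in expectation. A reader might also extend the problem to the main result. The article does not support that: 7-day abstinence and PHQ-9 are analysed from end of treatment onwards and use no event clock.

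**Conclusion.** The point holds for time to first lapse, a secondary outcome under hypothesis 1b. The article fixes a clock that starts a week before the arms can differ, and nothing in it removes the pre-allocation events. The result is a hazard ratio pulled towards 1 and lost power.

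The direction is certain whenever treatment has an effect and some participants lapse in week 1. The size is not: power falls by 4 to 8 points under a true HR of 0.80 and by 4 to 26 points under 0.70, over assumed week-1 shares of 10% to 50%.

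It would be wrong to treat all three hypothesis 1b outcomes alike. Relapse can hardly be completed before randomisation. For continuous abstinence the risk difference shrinks by the share lapsed, but the odds ratio moves only from 1.44 to between 1.41 and 1.34. A worthwhile, inexpensive improvement to the secondary analyses.

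**What to change.** - **First lapse.** For the between-arm test, start the clock at randomisation, or use delayed entry at randomisation, among participants with no smoking since discharge at Baseline 2. State this as an exception to the all-randomised rule in the Missing data section.
- **Relapse.** Start the clock at randomisation and adjust for, or stratify by, Baseline 2 smoking status. Removing only those already relapsed would keep people who smoked through much of week 1 and can meet the definition within days.
- **Continuous abstinence.** Keep the from-discharge definition. Add an analysis of abstinence from randomisation, adjusted for Baseline 2 smoking status. It answers a different question, since someone who smoked in week 1 can count as abstinent.
- **Reporting.** Give the from-discharge time-to-event results as descriptive or sensitivity analyses, with the number who lapsed before randomisation in each arm.

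**Cost.** A change of definition in the analysis plan, best made before unblinded data are seen. Table 1 already collects the smoking data. For participants enrolled after discharge, smoking since discharge has to be put together from Baseline 1 and Baseline 2. The downside is that participants already smoking at randomisation leave the first-lapse analysis; they stay in the primary analysis.
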